### Inclusion criteria: virtual ward patient admission criteria

Consecutive patients under the home dialysis programs (PD and HHD) are admitted to the VW because of anyone of the following:

1. Discharge from hospital following an inpatient admission.

2. Medical procedure (e.g. access procedure).

3. Treatment with antibiotics.

4. Completion of home dialysis training program.

### Exclusion criteria

Patients are excluded from the virtual ward admission if they refuse to provide consent, or are unable to participate (e.g. language barrier).

### Outcome measures

The modified Charlson Comorbidity Index will be used to measure our patients’ case-mix [21]. Additional co-morbidities will also be recorded. The symptom assessment component is based on the validated Modified Edmonton Symptom Assessment Scale [22] and will be supplemented to include the 11 most common symptoms associated with ESRD [23]. The symptom scale also includes a free-form option for patients to report additional symptoms as recommended by Davison [24]. Each home dialysis patient is given a hardcopy symptom reference form. This form includes a visual analog scale that can be referred to at home during administration of the standardized patient assessment tool. This is done to maximize the ease of understanding of the symptom questions and rating scale. All patient materials are designed at a 6^th^ grade level. Aggregate demographic and symptom prevalence data will be presented (Additional file 1).

### Patient satisfaction survey

The Patient satisfaction questionnaire was developed to measure patient opinion regarding this new model of care. The measurement tool was modeled on a similar survey by Juergensen et al. [4], which was fine-tuned using the same iterative process as described for the standardized patient assessment tool. This questionnaire is organized into 4 distinct sections. Section 1 collects demographic information; Section 2 measures the impact of the VW on overall health and likelihood of requiring (re)admission to hospital; Section 3 asks questions about potential ‘coordination of care’ benefits; and, the last section pertains to domains of patients’ personal lives that were thought to be impacted by admission to the virtual ward. A hardcopy questionnaire will be given to all patients upon VW discharge. The questionnaire will be returned anonymously in a postage-paid envelope provided to encourage honest responses.

### Primary outcome

Our primary outcome is to identify the number of care gaps and interventions that the HDVW achieved.

### Secondary outcomes

Our secondary outcomes will include:

1. Within subject differences in symptoms score at baseline and at discharge of VW.

2. Number of re-hospitalizations

3. Rate of re-hospitalization

4. Patient satisfaction

5. Patient encounter time (per VW admission)

6. Stratification of care gaps which are associated with re-hospitalization

7. The VW re-hospitalization rate will be compared to the hospitalization rate of a contemporary cohort (matched for age, gender, renal replacement therapy and co-morbidities).

Admission to the VW will be described in absolute terms and expressed as proportion of total patients admitted per week. Travel time to home dialysis unit and whether the dialysis is performed independently or dependently is ascertained from the patient and/or primary nurse. Dialysis independency is defined as self-reliance on the following three domains: dialysis setup and equipment maintenance, cannulation or catheter access, and dialysis therapy management.

Identification of gaps in care will be assessed by measuring discrepancies between prescribed versus delivered management strategies documented at entry to the VW. Gaps in care will be categorized as 1. Changes to dialysis prescription; 2. Coordination of care; 3. Medication changes; and 4. Symptoms management. The percentage of VW patients with identifiable gaps in care and the types of gaps will be described. We will also stratify the types of care gaps which are associated with re-hospitalization.

Rates of hospital re-admission, un-scheduled home dialysis unit, emergency room, and in-center backup visits will be recorded prospectively for a planned 3-month period and expressed as health-services utilization rates per patient-year. Re-hospitalization rates will be compared before and after the intervention within each home dialysis program.

VW re-hospitalization rate will be compared to the hospitalization rate of a contemporary incident ESRD patient cohort through an existing collaborative effort by Oliver et al. [25]. The cohorts will be matched for age, gender, renal replacement therapy and co-morbidities (Figure 1).

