## Background

Patients with end-stage renal disease (ESRD) have a high burden of co-morbidity. The most common renal replacement therapy (RRT) in North America is conventional, thrice weekly, in-center hemodialysis (CHD). Home dialysis modalities (peritoneal dialysis (PD) and home hemodialysis (HHD)) are comparably under-utilized, but RRT in the home setting offers greater quality of life [1,2], higher patient satisfaction [3,4] and several other clinical advantages, including better survival compared to CHD [5-10].

These clinical advantages coupled with greater cost-efficacy have made expansion of home dialysis programs a mandate for many healthcare providers [1,11]. Although factors influencing technique failure and recruitment challenges to home dialysis have been examined previously [12-14], the absolute growth of home dialysis remains modest. The underlying reasons for inflow and outflow of patients through home dialysis programs suggest a role for interventions, which may enhance benefits and allay concerns [15]. Conceptually, an innovative care model that provides support to patients would improve retention by decreasing preventable causes of attrition and might also enhance recruitment through improving quality of support of the chronically ill at home.

Periods of transition from acute care to other settings are thought to represent a window of exaggerated patient vulnerability [16,17]. This is because several aspects of the care plan for complex patients may have changed during hospitalization [18,19]. Multiple categories of risk are prevalent during such transitions. These include changes in medication type, dosing and interaction issues, susceptibility to nosocomial infections, confusion regarding follow up, and failure to communicate with primary care providers. This subtlety is not lost on dialysis patients, who rate coordination of care between nephrologists and other physicians lower than other domains of patient satisfaction [3].

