## Discussion

This report describes the design, implementation and study protocol for the HDVW. We believe that the home dialysis patient population is uniquely poised to benefit from this intervention given that our patients are medically complex and commonly receive care from multiple providers. We chose to target our intervention to periods of care transitions, which is an interval of particular vulnerability [16,17]. We hypothesize that gaps in care are common in this setting and aim to develop a systematic description of these issues.

Intensive attention to care gaps in a vulnerable patient population may be predicted to have a number of salutary effects. Two prior randomized studies have shown that multi-disciplinary hospital avoidance schemes can be effective [16,26]. Naylor et al. randomized 363 frail elderly patients to comprehensive discharge planning and home follow-up by gerontology specialist advanced practice nurses (APN) versus standard discharge planning [26]. APNs used joint clinical decision making with physicians in this model. Patients allocated to the APN group had a 16.8% absolute reduction in re-admissions after 24 weeks and consumed approximately $600,000 less in medicare reimbursement charges. Coleman et al. studied high-risk elderly patients [16]. This trial randomized 750 patients to an intervention arm featuring a “transition coach” versus standard discharge planning. Similar to the Naylor study, the transition coach was an APN. The intervention focused on four domains including assistance with medication self-management, use of a patient-owned health record, timely follow-up with physicians, and identifying individualized “red flags”, indicative of a worsening condition. APNs coached patients on these goals before discharge as well as during a home visit and subsequent telephone conversations spanning 28-days post discharge. The adjusted odds ratio of re-admission was 0.64 (95% CI, 0.42-0.99; p = 0.04) at 90 days. The transition coach saved an estimated $300,000 per year by reducing re-admissions.

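### Secondary outcome 7 compares a rate measured after a trigger event with a general hospitalization rate that requires no trigger, so the ratio cannot be read as a virtual ward effect

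*Protocol article*

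**What the plan says.** The Secondary outcomes section of the protocol article lists as item 7: "The VW re-hospitalization rate will be compared to the hospitalization rate of a contemporary cohort (matched for age, gender, renal replacement therapy and co-morbidities"). Later in the same section the comparator is described more fully: "VW re-hospitalization rate will be compared to the hospitalization rate of a contemporary incident ESRD patient cohort", followed by "The cohorts will be matched for age, gender, renal replacement therapy and co-morbidities". Those four factors are the only matching variables named.

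The inclusion criteria admit a patient to the VW on any one of four events. The first is "Discharge from hospital following an inpatient admission" and the second "Medical procedure (e.g. access procedure"). The other two are antibiotic treatment and finishing home dialysis training.

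Secondary outcomes plans 3 months of prospective recording, expressed per patient-year. The Abstract places the follow-up calls at 2, 4 and 12 weeks after discharge from the VW, and The virtual ward intervention section plans a 14-day stay. The Background gives the reason for intervening at this time: "Periods of transition from acute care to other settings are thought to represent a window of exaggerated patient vulnerability".

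**The concern.** The two rates differ in three ways that the matching does not address. One counts re-hospitalizations and the other hospitalizations. One runs from a trigger event, while the other has no required index event. One covers a short window chosen because risk is thought to be raised, while the other is described only as a cohort's rate.

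The four matching factors describe the patient and not the moment. Two patients can agree on all four and still be at very different risk if one left hospital last week. The two rates could therefore differ even if the VW did nothing, and a VW that worked could look ineffective. This is the only external comparison planned for re-hospitalization, and the closing summary of the Discussion names hospital re-admission among the three effects that the study targets. The before-and-after comparison within each program is a separate analysis and does not repair this one.

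**Working it through.** **The plan's own figures.** The Implementation section expects at least 40 events in 200 patients, from 76 events in 400. The check is 200 × 76/400 = 38, close to the stated 40. No effect size, power or test is given for secondary outcome 7, so there is no planned figure for this contrast to reproduce.

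The Discussion reports a transition-coach trial: "The adjusted odds ratio of re-admission was 0.64 (95% CI, 0.42-0.99; p = 0.04) at 90 days". Its figures agree with each other. SE = (ln 0.99 − ln 0.42)/(2 × 1.96) = 0.219; z = |ln 0.64|/0.219 = 2.04; two-sided p = 0.041.

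**Formula.** Let k be the rate that VW patients would have had after their trigger without the VW, divided by the comparator's rate. Then

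observed rate ratio = k × true rate ratio.

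The documents do not give k, so it is varied here on both sides of 1.

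**An illustrative true effect.** For a control 90-day risk p, an odds ratio of 0.64 gives an intervention risk q with q/(1 − q) = 0.64 × p/(1 − p). The rate ratio is ln(1 − q)/ln(1 − p). The risk p is assumed:

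- p = 0.20: q = 0.138, rate ratio 0.665
- p = 0.30: q = 0.215, rate ratio 0.680
- p = 0.40: q = 0.299, rate ratio 0.696

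A value of 0.67 is used below. It comes from high-risk elderly patients and only illustrates the arithmetic.

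**Result.**

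| k (assumed) | Observed if the VW has no effect | Observed if the true ratio is 0.67 |
|---|---|---|
| 0.8 | 0.80 | 0.8 × 0.67 = 0.54 |
| 1.0 | 1.00 | 0.67 |
| 1.5 | 1.50 | 1.5 × 0.67 = 1.0 |
| 2.0 | 2.00 | 2 × 0.67 = 1.3 |

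For k above 1, the VW must cut the rate by 1 − 1/k merely to look equal: 33% at k = 1.5 and 50% at k = 2. For k = 0.8, a VW with no effect would appear to cut the rate by 20%.

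**Mixture of triggers.** If a share s of entrants come from hospital discharge with ratio k_d, and the rest have ratio 1, the average is k = s × k_d + (1 − s). With s = 0.5, k_d = 2 gives k = 1.5 and an observed ratio of 1.0. With s = 0.5, k_d = 3 gives k = 2.0 and an observed ratio of 1.3. The share s is not given either.

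**The case against.** The strongest reply is that the direction of the bias is not established. The comparator is "the hospitalization rate of a contemporary incident ESRD patient cohort". Its person-time may include the start of dialysis, with admissions, access procedures and training of its own. That would pull k down, possibly below 1. A reader might infer from the article that comparator patients had no trigger, or that the contrast as a whole is biased against the VW. The text supports neither: it says only that no trigger is required. The Background premise concerns leaving acute care. The article also extends vulnerability to VW patients generally, but it nowhere quantifies it for antibiotics, procedures or completed training. This part of the objection stands.

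The VW clock is also not firmly fixed. If the 3 months start at VW discharge, about 14 days after entry, some early excess risk has already passed and k is smaller. This stands too.

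A third reply is that the comparator's index date and extraction window belong in a fuller protocol or analysis plan, and that Figure 1, which is not shown, may say more. An unstated window alone would indeed be no finding. But the article does state the two quantities to be compared and the matching factors, and as stated they are not like for like. The sentence that cites the figure names only the four factors.

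Finally, this is the last of seven secondary outcomes in a pilot. The primary outcome counts care gaps and interventions, the enrolment target does not rest on this contrast, and no decision is tied to it. That limits the severity.

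**Conclusion.** The mismatch is in the stated comparison and should be fixed. For patients who enter after a hospital discharge, the protocol's own premise makes bias against the VW likely. For the other entrants, and given an incident comparator, the size and even the direction of the bias cannot be determined from the article. With a true ratio of about 0.67, the observed ratio runs from 0.54 to 1.3 as k goes from 0.8 to 2. That range covers a flattering result, a null result and apparent harm, so the contrast cannot be read as a VW effect.

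It would be too strong to conclude that an effective VW will be reported as harmful. That needs k well above 1 across the whole mix of entrants, which nothing in the article establishes. The figures rest on an assumed range for k, an assumed 90-day risk of 20% to 40%, and an effect borrowed from a different population.

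**What to change.** Reword secondary outcome 7 so that the external contrast is restricted to VW patients who entered after a hospital discharge:

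- Match each of them to comparator patients at a hospital discharge, on the same four factors.
- Exclude from the comparator anyone under the VW.
- Start the clock at the same point in both groups, either at discharge or at the same lag after it.
- Count hospitalizations over the same 3 months in both groups.
- Draw any external conclusion about re-hospitalization from this contrast.

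Report patients who entered by procedure, antibiotics or training descriptively, unless the cohort records those triggers. Restricting to post-discharge entrants also gives every re-hospitalization an index admission, which the other entry routes do not supply.

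The change costs protocol wording and a different extraction from the cohort already planned. It relies on that cohort holding discharge dates, which is plausible for a source of hospitalization rates but is not stated. The contrast will also have fewer patients, and the article does not give the share of entrants who come from hospital discharge, so the loss of precision cannot be stated.

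### Secondary outcome 7 compares a re-hospitalization rate after a trigger event with the general hospitalization rate of an incident ESRD cohort not matched on that event or on dialysis vintage

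*Protocol article*

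**What the plan says.** The Secondary outcomes section of the protocol article lists the comparison as item 7 and repeats it in its last paragraph: "VW re-hospitalization rate will be compared to the hospitalization rate of a contemporary incident ESRD patient cohort". The next sentence gives the matching: "The cohorts will be matched for age, gender, renal replacement therapy and co-morbidities". The abstract names the same four factors.

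Entry to the VW needs an event. Under the admission criteria, "Consecutive patients under the home dialysis programs (PD and HHD) are admitted to the VW because of anyone of the following", and the list then gives four routes. The first is "Discharge from hospital following an inpatient admission", the fourth is "Completion of home dialysis training program", and between them stand a medical procedure and treatment with antibiotics.

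The Background gives the reason for choosing such moments: "Periods of transition from acute care to other settings are thought to represent a window of exaggerated patient vulnerability". The Discussion says that this was deliberate: "We chose to target our intervention to periods of care transitions, which is an interval of particular vulnerability".

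Utilization events, including re-admissions, "will be recorded prospectively for a planned 3-month period and expressed as health-services utilization rates per patient-year". The only other planned comparison of rates is before versus after the intervention within each home dialysis program.

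**The concern.** A rate ratio between two cohorts can be read as an effect of the VW only if both rates count the same event, from a comparable starting point, in patients with similar underlying risk. Here one side is the rate of a further admission in patients selected at a trigger. The other is the admission rate of an incident cohort for which no trigger is named. The four matching factors do not capture a recent discharge, the time since it, or time on dialysis.

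The label is a second difficulty. Re-hospitalization presupposes an earlier admission. Someone who enters after training, and possibly after antibiotics or an outpatient procedure, may have had none, yet the plan uses a single VW rate.

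What is at stake is the only comparison with an external concurrent group. The summary paragraph of the Discussion names hospital re-admissions among the things the study targets, and the within-program before-after comparison has no concurrent control.

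**Working it through.** **1. The two sides of the comparison as stated.**

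| | VW patients | Comparator |
|---|---|---|
| Who | Consecutive home dialysis patients with one of four triggers; no restriction on time since starting dialysis | Incident ESRD patients; no trigger named |
| Quantity | Re-hospitalization rate | Hospitalization rate |
| Matched on | Four factors | The same four factors |
| Not matched on | Entry event, dialysis vintage | Entry event, dialysis vintage |

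The finding rests on this table. The arithmetic below only shows what could follow.

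**2. The plan's own figure.** The Implementation section scales 76 adverse events in 400 general medicine patients to 200 home dialysis patients: 200 × 76/400 = 38, against a stated minimum of 40. That agrees, given the argument that ESRD patients are more complex. It concerns adverse events and does not size the between-cohort comparison.

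**3. Effect of the entry event alone (assumptions; the document gives none of these inputs).** Let s be the share entering by hospital discharge and k their rate over the follow-up window relative to the comparator, with the other routes at 1. With no VW effect the expected rate ratio is R = s·k + (1 − s).

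| s | k = 2 | k = 3 |
|---|---|---|
| 0.25 | 1.25 | 1.50 |
| 0.50 | 1.50 | 2.00 |
| 0.75 | 1.75 | 2.50 |

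**4. Effect of incident status (assumption).** Suppose instead that k is measured against established patients, and that the incident cohort is hospitalized at v times their rate. Then R is divided by v. With v = 1.5: 1.25/1.5 = 0.83, 1.50/1.5 = 1.00 and 2.50/1.5 = 1.67. The built-in ratio can fall below, at or above 1, so the direction is open.

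**5. What a real effect would look like.** The Discussion cites an adjusted odds ratio of 0.64 for re-admission in the transition-coach trial. Read as a rate ratio (an approximation), it would appear as:
- 0.83 × 0.64 = 0.53, benefit exaggerated;
- 1.25 × 0.64 = 0.80, benefit diluted;
- 2.00 × 0.64 = 1.28, apparent harm.

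It is fully hidden at R = 1/0.64 = 1.56.

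**6. Chance of a significant difference with no VW effect.** Assume a two-sided 5% test of two Poisson rates, a 1:1 matched cohort, 200 × 0.25 = 50 patient-years per group, and a comparator rate of 0.5 to 1.5 per patient-year. The standard error of the log ratio is √(1/e₀ + 1/e₁), where e₀ and e₁ are the expected events. For a rate of 1.0 and R = 1.5: e₀ = 50, e₁ = 75, SE = √(0.0200 + 0.0133) = 0.183, ln 1.5/SE = 2.22, and the chance is about 60%. Over the assumed rates:
- R = 1.25: 13% to 30%;
- R = 1.5: 35% to 78%;
- R = 2.0: 81% to 99.8%.

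If both groups start at the same kind of event and are alike in vintage, R = 1.00 as far as these two factors go, and the chance returns to 5%.

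**The case against.** The strongest case on the other side is about weight and certainty. This is the last of seven secondary outcomes in a pilot presented as proof of concept. The primary outcome, the number of care gaps and interventions, does not depend on it, and the article attaches no test or decision rule to it. All of that stands and limits the severity.

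Several stronger readings are tempting, and the document does not support them:
- **That the bias runs against the VW.** The vulnerability premise points that way, but incident patients may themselves be admitted more often, and vintage is unmatched. Step 4 shows that the sign can change.
- **That all VW patients enter at a high-risk event.** The Background ties exaggerated vulnerability to transitions from acute care. The Discussion speaks of care transitions broadly, but nothing shows that completed training or every antibiotic course carries high risk.
- **That the result would reflect the mix of entry routes and not the VW.** A VW effect multiplies whatever ratio is built in. The result mixes the two.
- **That events are ascertained differently in the two groups.** The article does not describe how the comparator's events are recorded, so this cannot be judged.

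It may also be said that index dates and cohort construction belong in the full protocol, and the study flow figure is not available here. That is fair for the comparator's start date, on which the article is silent. It does not answer the main point: the article itself states which two rates are compared, which cohort supplies the second, and which four factors are matched.

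**Conclusion.** The point holds as a should-fix on a secondary outcome. As written, secondary outcome 7 sets two different quantities against each other in groups not matched on entry event or dialysis vintage, so the ratio is confounded by both. The label re-hospitalization does not fit entrants without a prior admission.

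Net direction and size cannot be determined from the document. The built-in ratios of 1.25 to 2.5 (entry event alone) and 0.83 to 1.67 (with a 1.5-fold rate in the incident cohort) rest on assumed shares and multipliers. They show that a distortion as large as a plausible VW effect is possible either way, not that it will occur. The primary outcome and the enrollment target are untouched.

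**What to change.** Rewrite secondary outcome 7 and the last paragraph of the Secondary outcomes section so that:
- the between-cohort re-hospitalization comparison includes only VW patients admitted after hospital discharge, against comparator patients who were also discharged from hospital;
- follow-up starts at discharge in both groups and covers the same 3-month window. If VW entry lags discharge, require comparators to have stayed out of hospital for the same number of days;
- dialysis vintage is added to the matching factors or adjusted for;
- entrants by procedure, antibiotics or completed training are reported separately and descriptively, as hospitalization.

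If the collaborative data cannot identify hospital discharges, drop the between-cohort comparison and report the VW rate descriptively.

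Matching on all four triggers is not asked for, because nothing in the article shows that the comparator data record antibiotic courses, procedures or training. The cost is a revised data request and matching specification, with no new patients. The downside is a smaller comparison set than the 200 patients enrolled, and so less precision. The change should be made before comparators are drawn.
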